### Outcomes

The primary efficacy end point is proportion of patients with successful MeVO recanalization, defined as the expanded treatment in cerebral ischemia (eTICI) score 2b67-3 in the territory of the target occluded MeVO artery. (18)

The secondary efficacy end points are as follows: (1) proportion of modified Rankin Scale (mRS) 0–1 at 90 days; (2) proportion of mRS (0–2) at 90 days; (3) distribution of mRS at 90 days; (4) incidence of early neurological improvement (ENI), defined as a decrease of more than four points or reaching zero points in NIHSS score, compared with baseline at 24 (−6/+24) hours; (5) change in NIHSS compared with baseline at 24 (−6/+24) hours; (6) rate of visual recovery in patients with posterior cerebral artery occlusion at 7 days or at hospital discharge, whichever is earlier (categorized as no recovery, partial recovery and complete recovery).

The primary safety end point is the proportion of symptomatic intracranial hemorrhage (sICH) within 24 (−6/+24) hours, which is defined as an increase in the NIHSS score of ≥4 points as a result of the intracranial hemorrhage (19).

The secondary safety end points include proportion of parenchymal hematoma type 1 and 2 (PH1 and PH2) at 24 (−6/+24) hours, all serious adverse events at 24 (−6/+24) hours, all-cause death within 7 ± 2 days or during hospitalization and proportion of recurrent stroke, cardiovascular events, other vascular events and death within 90 days.

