### Study population

In the RESCUE-TNK trial, eligible participants are AIS patients with primary MeVO detected by the first DSA, or secondary MeVO after mechanical thrombectomy. Patients will be enrolled at approximately 20 sites in China between March 2023 and March 2025. The detailed inclusion/exclusion criteria are listed in Table 1. Specifically, intravenous thrombolysis should be administrated within 270 min according to current guidelines.

**Table 1 tab1:** Inclusion/exclusion criteria.

Inclusion criteria:
Age ≥ 18 years;
Medium vessel occlusion (MeVO), referring to M2-3 of MCA; A1-3 of ACA; P1-3 of PCA; PICA, AICA or SCA (including primary, distal embolism in the same region after thrombectomy or concurrent embolism in other regions).
Primary MeVO as detected by the first DSA examination or secondary MeVO after mechanical thrombectomy for large vessel occlusion;
MeVO causes neurological deficits in motor strength, language, vision etc.;
Endovascular mechanical thrombectomy cannot be performed as assessed by the investigator;
Absence of parenchymal hematoma on CT images performed in the angio suite.
Within 24 h from symptom onset;
Signed informed consent by patient or patient’s legally authorized representative.
Exclusion criteria:
Patients with completed infarction in the territory of the MeVO on non-contrast CT;
Patients with intracranial hemorrhage;
Coagulation disorders, tendency for systemic hemorrhagic, thrombocytopenia (<100,000/mm^3^);
Severe hepatic or renal dysfunction, increase in ALT or AST (more than 2 times of upper limit of normal value), increase in serum creatinine (more than 1.5 times of upper limit of normal value) or requiring dialysis;
After mechanical thrombectomy, severe and sustained (> 5 min) uncontrolled hypertension (systolic blood pressure over 180 mmHg or diastolic blood pressure over 105 mmHg);
Patients with contraindication or allergy to any ingredient of study medication;
Pregnancy, plan to get pregnant or active lactation;
The estimated life expectancy is less than 6 months due to other serious diseases;
Other conditions unsuitable for this clinical study as assessed by researcher.

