### Follow-up procedure

Study visits will be performed at 24 (−6/+24) hours, 7 ± 2 days, and 90 ± 7 days after randomization (Figure 1). At baseline, demographic characteristics, pre-stroke mRS, NIHSS, routine laboratory tests, and neuroimaging including CT perfusion data if performed will be recorded. At 24 h, a repeat non-contrast CT + CTA/MRI + MRA will be performed for both groups. NIHSS scoring will be repeated at 24 (−6/+24) hours, 7 ± 2 days, and mRS will be assessed at 90 ± 7 days. All clinical assessments including NIHSS and mRS will be evaluated by certified assessors according to a standardized procedure manual at each site. An anterior-posterior (AP) and the lateral view will be obtained on all angiographic runs for the site of MeVO occlusion at baseline and the end of the procedure. The primary endpoint (eTICI scores) will be initially assessed by the local investigator and later adjudicated by a central neuroimaging lab blinded to treatment allocation. To prevent bias, the 90-day clinical assessments including mRS will be evaluated by one qualified personnel blinded to treatment allocation. To ensure the validity, consistency, and reproducibility of the evaluation, we will have a training course for all investigators at each center. MRS at 90 days will be evaluated in person or by telephone interview if an in-person evaluation is not possible. Adverse events within 90 days of randomization will be recorded in detail by investigators. The cycle of this research is expected to be approximately 24 months.

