### Statistical analysis

An intention-to-treat (ITT) analysis will be used to analyze the therapeutic effects of the two groups and all data will be analyzed with SPSS 20.0 Software. The mean ± standard deviation (SD) will be used if the data are normally distributed; the median and interquartile range (IQR) will be used if the data are not normally distributed. Differences in the proportion of successful recanalization of MeVO (eTICI score 2b67-3 for the target vessel), mRS (0–1) at 90 days, mRS (0–2) at 90 days, and ENI will be compared using binary logistic regression. The distribution of the mRS at 90 days between the two groups will be compared using ordinal logistic regression. Time-to-events of stroke recurrence and other vascular events will be compared using Cox regression. The change in NIHSS score within 48 h between the two groups will be compared using a general linear model. All statistical tests are 2-sided, using *α* = 0.05 and *p* < 0.05 as considered statistically significant.

The subgroup for primary endpoint will be performed by age, sex, different doses of TNK, type of MeVO, NIHSS score at presentation, time from onset to randomization, whether intravenous thrombolysis, stroke territory, and stroke etiology.

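### Fixed mRS 0–1 and 0–2 cut-points, with no pre-stroke disability limit at entry, make patients with prior disability near-certain failures and attenuate two secondary comparisons

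*Protocol article*

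**What the plan says.** **End points.** Under Outcomes, the first secondary efficacy end point is "proportion of modified Rankin Scale (mRS) 0–1 at 90 days". The next two are "2) proportion of mRS (0–2) at 90 days; (3) distribution of mRS at 90 days". The two proportions use absolute cut-points, and no clause refers to the patient's level before the stroke.

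**Eligibility.** Under Study population, the article states that "The detailed inclusion/exclusion criteria are listed in Table 1". That table contains no pre-stroke mRS or prior-disability criterion. Entry is open to adults with no upper age limit. The two nearest exclusions are "The estimated life expectancy is less than 6 months due to other serious diseases" and "Other conditions unsuitable for this clinical study as assessed by researcher". The first concerns survival, and the second is open judgement without an mRS threshold.

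**Data.** Under Follow-up procedure, the baseline record includes "pre-stroke mRS, NIHSS, routine laboratory tests", so the pre-stroke level is available for every patient.

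**Analysis.** Under Statistical analysis, the two mRS proportions are compared by binary logistic regression, and "The distribution of the mRS at 90 days between the two groups will be compared using ordinal logistic regression". No covariates are listed for any model.

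**The concern.** The eligibility table and the end-point definitions are each conventional. Together they create a group of patients whose result on a binary end point is all but settled before randomization. Someone living at mRS 2 before the stroke can at best be expected to return to mRS 2, and on mRS 0–1 that is a failure. Someone at mRS 3 fails mRS 0–2 as well.

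The article's hypothesis is that opening the vessel will in turn improve clinical outcome, and the 90-day mRS end points are its main functional test of that step. With 40 patients per arm these comparisons are already weak. Patients who cannot succeed in either arm weaken them further, although the variable needed to avoid this is being collected.

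The article handles a similar problem differently elsewhere in the same list. Its definition of early neurological improvement also counts an NIHSS of zero as success, so a patient with a low starting score can still succeed. The mRS proportions have no matching clause.

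**Working it through.** **Step 1: the plan's own figure.** Sample size determination assumes recanalization of 20% v 50%, 80% power and one-sided α = 0.025. With unpooled variance:

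n per arm = (0.2 × 0.8 + 0.5 × 0.5) × (1.960 + 0.842)² / 0.30² = 35.8, so 36 per arm and 72 in total. Allowing for 10% loss, 72 / 0.9 = 80.

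The stated 72 and 80 reproduce. They concern an angiographic end point that pre-stroke mRS does not enter, so this point leaves them unchanged.

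**Step 2: inputs for mRS 0–1.**
- 40 per arm: Sample size determination.
- Two-sided α = 0.05: Statistical analysis.
- Success rates among patients able to reach mRS 0–1, 65% v 45%: assumption, not in the documents.
- Share f with pre-stroke mRS ≥ 2, 5% to 20%: assumption, not in the documents.

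**Step 3: dilution.** If a share f in each arm cannot succeed, the expected rates are (1 − f) × 0.65 and (1 − f) × 0.45, and the difference is (1 − f) × 0.20. Power is the normal approximation with pooled variance under the null:

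Power = Φ[(difference − 1.96 × SE₀) / SE₁], where SE₀ = √(2p̄(1 − p̄)/40) and SE₁ = √((p₁(1 − p₁) + p₂(1 − p₂))/40).

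Example at f = 0.20: the rates are 52% v 36%, the difference is 0.16, SE₀ = 0.1110 and SE₁ = 0.1095. Power = Φ[(0.16 − 0.2176)/0.1095] = Φ(−0.53) ≈ 0.30.

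| f | Rates | Difference (points) | Power |
|---|---|---|---|
| 0 | 65.0% v 45.0% | 20 | 43% |
| 5% | 61.8% v 42.8% | 19 | 40% |
| 10% | 58.5% v 40.5% | 18 | 36% |
| 15% | 55.3% v 38.3% | 17 | 33% |
| 20% | 52.0% v 36.0% | 16 | 30% |

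**Step 4: sensitivity to the assumed rates.** With 50% v 30%, power goes from 44.5% (f = 0) to 38.7% (f = 10%) and 33.3% (f = 20%). With 60% v 40% it goes from 43.1% to 36.4% and 30.6%. The factor (1 − f) on the difference does not depend on the rates chosen.

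**Step 5: the other mRS end points.** For mRS 0–2 the same formula applies, but f is then the share with pre-stroke mRS ≥ 3, which cannot exceed the share with ≥ 2. In the ordinal analysis the range open to these patients is truncated, but they still contribute.

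**Step 6: what a return-to-baseline clause recovers.** Let the group with prior disability return to its pre-stroke level at rates that differ by d between arms. The overall difference becomes (1 − f) × 0.20 + f × d. At f = 0.20:
- d = 0.20 gives 0.16 + 0.04 = 0.20, full recovery.
- d = 0.10 gives 0.16 + 0.02 = 0.18.
- d = 0 gives 0.16, no gain in the difference.

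**The case against.** **Fixed cut-points and broad entry are legitimate choices.** mRS 0–1 and 0–2 are conventional, and the Discussion presents wide inclusion as a strength. This stands as an argument against restricting entry, and no restriction is proposed. It does not answer the end-point definition, which can be suited to a broad population without excluding anyone.

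**Covariates belong in the analysis plan.** This stands. The article names model types only, and an analysis plan not shown may adjust for pre-stroke mRS. The missing covariate is not the defect; adjustment is only part of the remedy.

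**A reader might infer that these patients tell us nothing about treatment.** The documents do not support that. They contribute fully to recanalization, early neurological improvement and NIHSS change, and they contribute to the ordinal mRS analysis. Patients at pre-stroke mRS 2 can also succeed on mRS 0–2.

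**A reader might infer that chance imbalance in their number adds a spurious difference.** At f = 15% a one-SD imbalance is √(80 × 0.15 × 0.85) = 3.2 patients, or about 3.2 × 0.55/40 = 4.4 points, where 0.55 is the mean of 65% and 45%. The standard error of the difference is about 11.0 points and already contains this component: (4.4/11.0)² is about 16% of its variance. The test allows for it, so it is neither bias nor an extra error.

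**The effect is modest and rests on assumptions.** This stands. At f of 5–10%, power moves only from 43% to 40–36%, on a secondary end point that is underpowered even at f = 0.

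**Conclusion.** The point holds in a limited form. As the article defines them, mRS 0–1 and mRS 0–2 score some patients as near-certain failures in both arms whatever happens to the index stroke: pre-stroke mRS ≥ 2 for the first, ≥ 3 for the second. Each absolute difference is attenuated by (1 − f). Under the assumed 65% v 45% and f of 5–20%, that costs 1 to 4 points of difference and roughly 4 to 13 percentage points of power on mRS 0–1. Neither the rates nor f can be checked against the documents.

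This worsens a comparison that is already weak; it does not cause the weakness. It is not systematic bias, and it does not affect the primary end point, its analysis or the sample size of 80. Priority is optional to low.

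**What to change.** 1. Under Outcomes, define success on the two binary end points as mRS 0–1 (respectively 0–2) at 90 days, or return to the recorded pre-stroke mRS.
2. Report the plain mRS 0–1 and mRS 0–2 proportions alongside, for comparison with other trials.
3. Adjust the binary and ordinal 90-day mRS models for pre-stroke mRS, unless the analysis plan already does so.
4. Leave eligibility unchanged.

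**Cost.** One clause in the definition and one covariate already collected at baseline ("At baseline, demographic characteristics, pre-stroke mRS, NIHSS, routine laboratory tests"); no new data are needed. Current status says recruitment had not begun at first submission, so the change was possible then before any outcome was known. If recruitment has since started, it should be dated and made before unblinded mRS data are seen.

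**Downsides.** There is a second line of results to report, and success in the composite means different levels of function for different patients. Attenuation is undone only as far as treatment helps patients with prior disability return to their earlier level.

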### Follow-up procedure

Study visits will be performed at 24 (−6/+24) hours, 7 ± 2 days, and 90 ± 7 days after randomization (Figure 1). At baseline, demographic characteristics, pre-stroke mRS, NIHSS, routine laboratory tests, and neuroimaging including CT perfusion data if performed will be recorded. At 24 h, a repeat non-contrast CT + CTA/MRI + MRA will be performed for both groups. NIHSS scoring will be repeated at 24 (−6/+24) hours, 7 ± 2 days, and mRS will be assessed at 90 ± 7 days. All clinical assessments including NIHSS and mRS will be evaluated by certified assessors according to a standardized procedure manual at each site. An anterior-posterior (AP) and the lateral view will be obtained on all angiographic runs for the site of MeVO occlusion at baseline and the end of the procedure. The primary endpoint (eTICI scores) will be initially assessed by the local investigator and later adjudicated by a central neuroimaging lab blinded to treatment allocation. To prevent bias, the 90-day clinical assessments including mRS will be evaluated by one qualified personnel blinded to treatment allocation. To ensure the validity, consistency, and reproducibility of the evaluation, we will have a training course for all investigators at each center. MRS at 90 days will be evaluated in person or by telephone interview if an in-person evaluation is not possible. Adverse events within 90 days of randomization will be recorded in detail by investigators. The cycle of this research is expected to be approximately 24 months.

### Data management and quality control

All data will be obtained by MedSci^1^ which includes the patient case report form. The data will be downloaded from MedSci with a dedicated person for statistical analysis. The data safety and monitoring committee (DSMC) will perform data review to monitor safety outcomes, such as hemorrhagic events and other adverse events (AEs), etc. A central core lab for imaging was set to judge intracranial bleeding events and assess neuroimaging data. An interim analysis will be conducted after 50% of patients have had their 90-day follow-up by an independent statistician of the DSMC, who is not involved in managing the trial. Based on this analysis, the DSMC can recommend to the Steering Committee to adjust the sample size or early termination of the study. As for the interim analysis, no formal analysis of the primary endpoint will be performed, to avoid the occurrence of a type-1 error in the final analysis.

### Adverse event monitoring

An AE is any adverse medical event that occurs during the study. All information about AEs should be recorded on the AE page of the case report, and whether the unexpected AE is associated with intra-arterial TNK treatment will be further adjudicated by the DMSB.

### Sample size determination

Subgroup analysis of PROACTII found that the reperfusion rate of intra-arterial thrombolysis for M2 occlusion was 53.6%, while that of the control group was 16.7%, (12) with a difference of 36.9%. Accordingly, we estimate that the proportion of recanalization of MeVO in the control group in this study will be 20%, while the proportion in the experimental group is conservatively estimated to be 50%, with a 30% increase. Using a power of 80% and *α* of 0.025 to carry out the one-side test, the calculated sample size is 72. In consideration of the 10% lost to follow-up, the total sample size is 80. Therefore, this study will include 80 patients, with 40 patients in each group.

### Statistical analysis

An intention-to-treat (ITT) analysis will be used to analyze the therapeutic effects of the two groups and all data will be analyzed with SPSS 20.0 Software. The mean ± standard deviation (SD) will be used if the data are normally distributed; the median and interquartile range (IQR) will be used if the data are not normally distributed. Differences in the proportion of successful recanalization of MeVO (eTICI score 2b67-3 for the target vessel), mRS (0–1) at 90 days, mRS (0–2) at 90 days, and ENI will be compared using binary logistic regression. The distribution of the mRS at 90 days between the two groups will be compared using ordinal logistic regression. Time-to-events of stroke recurrence and other vascular events will be compared using Cox regression. The change in NIHSS score within 48 h between the two groups will be compared using a general linear model. All statistical tests are 2-sided, using *α* = 0.05 and *p* < 0.05 as considered statistically significant.

The subgroup for primary endpoint will be performed by age, sex, different doses of TNK, type of MeVO, NIHSS score at presentation, time from onset to randomization, whether intravenous thrombolysis, stroke territory, and stroke etiology.

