## Discussion

As an effective treatment for LVO stroke, EVT is highly recommended by current guidelines. Some studies suggested the feasibility, safety, and possible benefit of EVT for MeVO, but the treatment may vary according to the patient’s anatomy, location, type of occlusion, available devices, and neurointerventionalist’ skills. Rescue intra-arterial thrombolysis has been found to be safe and effective for LVO, but its efficacy for opening a MeVO is unknown. Collectively, the ideal recanalization strategy for MeVO is unclear. (4, 20)

RESCUE-TNK is a prospective multicenter randomized trial investigating the efficacy and safety of intra-arterial TNK in patients with MeVO. In contrast to prior studies, this trial has several distinct characteristics. First, previous studies on MeVO reperfusion strategy mainly focused on mechanical thrombectomy, (4–9, 20, 21) with little regard to the effect of intra-arterial thrombolysis, which will be investigated in this trial. Second, most studies were single-center and retrospective, (22–24) while the prospective multicenter design is being used in this trial. Third, the M2 site of occlusion has been widely studied in previous MeVO studies, (7–9, 12) while this trial will enroll all MeVO patients, which will allow the study to be more inclusive of patients with medium or distal vessel occlusion in different locations. (25) The lack of requirement of perfusion imaging to select patients in this trial may permit the results to be more generalizable to centers that do not routinely use advanced imaging in their selection of patients for EVT. (25, 26) Fourth, TNK for intra-arterial thrombolysis will be used in this trial, given that TNK has greater fibrin specificity, higher reperfusion rates, and possibly better safety profile than alteplase. (27) Fifth, we did not set the lower limit of the baseline NIHSS score, given the disability of some MeVO patients with low NIHSS score (such as isolated aphasia and hemianopia), and early successful recanalization should be beneficial for this population who was judicated by local investigator. Finally, the unique intra-arterial thrombolysis strategy with doses adjusted to the patient’s clinical presentation will be used in this trial to balance the benefit and risk.

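### No baseline covariate is stated for NIHSS change or 90-day mRS, although baseline NIHSS and pre-stroke mRS are recorded; prespecifying adjustment would improve these secondary analyses at no data cost

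*Protocol article*

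**What the plan says.** All references are to the protocol article.

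- **Outcomes** lists, as a secondary efficacy endpoint, "change in NIHSS compared with baseline at 24" hours (window −6/+24). The 90-day mRS endpoints (0–1, 0–2, distribution) are also secondary.
- **Statistical analysis** assigns the models. For NIHSS: "The change in NIHSS score within 48 h between the two groups will be compared using a general linear model". For the mRS distribution: "The distribution of the mRS at 90 days between the two groups will be compared using ordinal logistic regression". Recanalization, mRS 0–1, mRS 0–2 and early neurological improvement share one sentence, which ends "ENI will be compared using binary logistic regression". No covariate is named for any model. Baseline severity appears only in the list of subgroup factors for the primary endpoint: "type of MeVO, NIHSS score at presentation, time from onset to randomization".
- **Follow-up procedure** shows that the data exist: "At baseline, demographic characteristics, pre-stroke mRS, NIHSS, routine laboratory tests, and neuroimaging including CT perfusion data if performed will be recorded".
- **Discussion**: "we did not set the lower limit of the baseline NIHSS score". Table 1 sets no NIHSS or pre-stroke mRS limit, and it admits both primary MeVO and MeVO secondary to thrombectomy for large vessel occlusion.
- **Randomization and intervention** names centre as the only factor in the minimization.

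**The concern.** A change score compared between two groups with no baseline term corrects for baseline with a fixed slope of 1. If the true slope of follow-up on baseline NIHSS is not 1, the comparison is noisier than it need be, and part of any chance difference in baseline severity stays in the estimate. A slope below 1 is plausible here, because a patient who starts with a low score has little room to fall.

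Three features make this relevant to the trial. Eligibility leaves baseline NIHSS and pre-stroke mRS open. Primary and secondary MeVO may differ in starting severity. No stated randomization factor balances severity between arms of 40. A wide baseline spread is an inference from these features; the article does not report one.

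For 90-day mRS, age, baseline severity and pre-stroke disability can be expected to be prognostic. Leaving them out of a logistic model costs power.

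**Working it through.** **The plan's own figure.** The sample size concerns recanalization, with 20% against 50%, 80% power and one-sided 0.025. With unpooled variance, n per arm = [0.2×0.8 + 0.5×0.5] × (1.960 + 0.842)² / 0.30² = 0.41 × 7.85 / 0.09 = 35.8, so 36 per arm and 72 in total. Then 72/0.9 = 80. The stated figures reproduce. They do not involve NIHSS or mRS, so nothing below alters them.

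**Inputs for the NIHSS comparison.** From the article: 40 per arm, two-sided 0.05. Not given, so assumed: the baseline-to-follow-up correlation r, from 0.3 to 0.8, and the ratio k of follow-up SD to baseline SD, from 1.0 to 1.5.

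**Formulas**, in units of baseline variance:

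- Variance of the change score: 1 + k² − 2rk
- ANCOVA residual variance: k²(1 − r²)
- Difference between the two: (1 − rk)², which is never negative. The gain is therefore zero only when rk, the slope of follow-up on baseline, equals 1.

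At k = 1 the ratio simplifies to (1 − r²)/(2(1 − r)) = (1 + r)/2.

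**ANCOVA variance divided by change-score variance:**

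| r | k = 1.0 | k = 1.2 | k = 1.5 |
|---|---|---|---|
| 0.3 | 0.65 | 0.76 | 0.87 |
| 0.5 | 0.75 | 0.87 | 0.96 |
| 0.6 | 0.80 | 0.92 | 0.99 |
| 0.7 | 0.85 | 0.97 | 1.00 |
| 0.8 | 0.90 | 1.00 | 0.95 |

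Example: r = 0.3, k = 1.2 gives 1.44 × 0.91 / (1 + 1.44 − 0.72) = 1.310/1.72 = 0.76.

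**In patients, k = 1.** An unadjusted change analysis needs 80/ratio patients to match ANCOVA on 80: 123, 107, 100, 94 and 89 at r = 0.3, 0.5, 0.6, 0.7 and 0.8.

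**In power, k = 1.** If ANCOVA had 80% power, the unadjusted change analysis would have Φ(2.802 × √ratio − 1.960): 68%, 71%, 73% and 76% at r = 0.5, 0.6, 0.7 and 0.8.

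**Chance imbalance.** The standard error of the difference in mean baseline NIHSS between arms of 40 is √(2/40) = 0.22 SD, so the 95% range is about ±0.44 SD. A change score carries (rk − 1) times the imbalance into the estimate. At k = 1 and r = 0.5, an imbalance of 0.44 SD shifts the comparison by 0.5 × 0.44 = 0.22 baseline SD. At slope 1 the shift is zero.

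**mRS models.** No comparable variance ratio applies. Covariate adjustment in a logistic or ordinal model does not shrink the standard error of the log odds ratio. It changes the target to a conditional odds ratio and may raise power. The documents give no figures from which to size this.

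**The case against.** The strongest objection is that silence is being read as a decision. The article never says unadjusted. Every model it names can carry covariates, and describing a comparison between two groups fits an adjusted model equally well. Covariate lists are commonly left to an analysis plan, which is not shown. This stands: a reader might infer that the trial will run unadjusted models, but the text does not establish that. What remains is that the article fixes the outcome form and the model for each endpoint, and gives baseline NIHSS only a subgroup role for the primary endpoint. A better specification can be stated at once.

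The second objection is that the size depends on assumptions. This also stands. Equal SDs favour adjustment; at k = 1.5 the gain is 0–5% for r of 0.5 or more. Larger gains could be produced by assuming a mix of low-scoring primary and high-scoring secondary MeVO, but the documents give neither the mix nor the scores.

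Other stronger readings also fail:

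- *Imbalance passes in full into the NIHSS result.* A change score already subtracts baseline, so only the fraction (rk − 1) remains, and the randomized comparison is unbiased either way.
- *Adjustment would let patients with prior disability reach mRS 0–1.* It would not; that concerns eligibility and endpoint choice and applies to both arms.
- *The primary recanalization model needs the same change.* Nothing here demonstrates a defect in it.

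**Conclusion.** The point holds as an improvement to secondary analyses, not as a demonstrated error. No baseline covariate is stated for NIHSS change or the 90-day mRS models, although suitable ones are collected, eligibility does not restrict them, and no stated randomization factor balances them.

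For NIHSS, the variance reduction is about 10–35% under equal SDs and r from 0.8 down to 0.3. It shrinks toward zero as a more variable follow-up brings the slope near 1. In large samples ANCOVA is never less precise. With 80 patients, estimating one slope uses one of 78 residual degrees of freedom (80 − 2), a cost of about 1%. For mRS the benefit is power and protection against chance imbalance, unquantified here, with a conditional odds ratio as the estimand.

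A reader might infer that a known amount of precision is lost, or that the trial is too small as a result. The documents support neither: they give no NIHSS SD or correlation, and the 80 patients were sized on recanalization.

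**What to change.** In Statistical analysis, state that:

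1. NIHSS at 24 hours (or its change) is analysed by ANCOVA with baseline NIHSS as a covariate. Either outcome form gives the same treatment effect once baseline is in the model.
2. The binary and ordinal models for 90-day mRS adjust for a short prespecified set already collected, such as age, baseline NIHSS and pre-stroke mRS, and the reported odds ratios are conditional on that set. With 40 patients per arm the set should stay short.
3. Unadjusted results are reported as sensitivity analyses.

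If the analysis plan already says this, a sentence confirming it is enough.

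The cost is wording only: no new data, visits or patients, and no change to the primary analysis. Current status reports that recruitment had not begun at first submission, so the set could have been fixed then without knowledge of the data. If it is not yet fixed, that should be done before anyone choosing the covariates sees outcomes by arm, including those in the planned interim review.

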### Randomization and intervention

Eligible patients will be assigned into an experimental group and a control group as a 1:1 ratio by using central and computerized random sequence generation (dynamic randomization-minimization) as stratified by center. The experimental group will be treated with intra-arterial (IA) TNK *via* a microcatheter proximal to the site of the occlusion for 20 to 30 min. TNK will be temporarily stopped at 20 min from the onset of infusion, at which time recanalization status will be adjudicated by DSA. If successful recanalization is not achieved, TNK will be administered for the remaining 10 min. Different doses of intra-arterial TNK will be given based on whether intravenous thrombolysis or rescue balloon angioplasty and/or stenting is performed: (1) 0.3 mg/min IA TNK if neither treatment was given; (2) 0.25 mg/min IA TNK if either of them was given; (3) 0.2 mg/min IA TNK if both treatments were given. The control group will be treated with routine therapy. Both groups of patients will be given standard care based on the guidelines. (16, 17)

During the first 24 h, we recommend that SBP will be tightly controlled to less than 180/100 mmHg and less than 140/90 mmHg if eTICI ≥2b67 is achieved; blood glucose level will be controlled to less than 160 mg/dl.

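### The planned subgroup by TNK dose has no value in controls, and dose follows from other treatments; a tier fixed at randomization in both arms should replace it

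*Protocol article*

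**What the plan says.** In the protocol article, Statistical analysis lists the subgroup factors for the primary end point: "The subgroup for primary endpoint will be performed by age, sex, different doses of TNK, type of MeVO". The rest of the list is presenting NIHSS, time from onset to randomization, intravenous thrombolysis, territory and etiology, which makes nine factors in all. No definition of the dose factor is given for control patients.

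Randomization and intervention explains where the doses come from: "Different doses of intra-arterial TNK will be given based on whether intravenous thrombolysis or rescue balloon angioplasty and/or stenting is performed". The three tiers are "0.3 mg/min IA TNK if neither treatment was given", "0.25 mg/min IA TNK if either of them was given" and "0.2 mg/min IA TNK if both treatments were given". Duration is governed separately: "TNK will be temporarily stopped at 20 min from the onset of infusion, at which time recanalization status will be adjudicated by DSA", and then "If successful recanalization is not achieved, TNK will be administered for the remaining 10 min". For the other arm, the section says: "The control group will be treated with routine therapy".

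**The concern.** A subgroup analysis of a randomized effect compares the two arms within each level of a factor, so every patient in both arms needs a value of that factor. The other eight listed factors can be recorded for everyone. TNK dose cannot, because controls receive none.

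An analyst applying the list literally has two options: compare doses with one another inside the TNK arm, or set each dose group against the whole control arm. Neither is a randomized comparison. The rate is determined by two other treatments, so patients at different rates differ in treatment history and possibly in prognosis. The Discussion presents the adjusted dosing as a distinctive feature of the trial, so readers are likely to look to this subgroup for evidence about dose. A trend across the three rates could be taken for a dose-response when it only reflects who was assigned to each rate.

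**Working it through.** **Inputs from the protocol article.** Success rates of 20% (control) and 50% (TNK), 80% power, one-sided alpha 0.025, 72 patients before and 80 after a 10% loss (Sample size determination). Rates of 0.3, 0.25 and 0.2 mg/min and durations of 20 or 30 min (Randomization and intervention).

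**The plan's own figure.** With unpooled variance, n per arm = (0.20×0.80 + 0.50×0.50) × (1.960 + 0.842)² / 0.30² = 0.41 × 7.85 / 0.09 = 35.8, rounded up to 36. The total is 72, and 72/0.90 = 80. The stated size is reproduced. The point does not rest on it, but the 20% and 50% are used below.

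**Dose read as infusion rate.** The tier shares and tier-specific control rates are assumptions, chosen so that the overall rates match the plan.

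| Tier | Share | Control | TNK (+30) | TNK minus all controls (20%) | TNK minus same-tier controls |
|---|---|---|---|---|---|
| Neither treatment, 0.3 mg/min | 40% | 28% | 58% | 38 points | 30 points |
| One, 0.25 mg/min | 40% | 18% | 48% | 28 points | 30 points |
| Both, 0.2 mg/min | 20% | 8% | 38% | 18 points | 30 points |

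Overall control rate: 0.4×28 + 0.4×18 + 0.2×8 = 11.2 + 7.2 + 1.6 = 20%. Overall TNK rate: 20 + 30 = 50%.

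The true effect is 30 points in every tier. Against all controls it appears to fall from 38 to 18. Inside the TNK arm, the highest and lowest rates differ by 58 − 38 = 20 points with no effect of dose at all. Same-tier controls recover 30 points each time.

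**Dose read as total dose or infusion time.** Total dose = rate × duration:
- 0.2 mg/min gives 4 or 6 mg
- 0.25 mg/min gives 5 or 7.5 mg
- 0.3 mg/min gives 6 or 9 mg

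The 6 mg level arises both from 0.3 × 20 and from 0.2 × 30, so it mixes tiers and mixes patients who were open at 20 min with patients who were not.

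Suppose a share p is open at 20 min and stays open, and final success is 50%. Success in the 30-min group is then (0.50 − p)/(1 − p):

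| p (assumed) | 30-min group | Minus 20% control rate |
|---|---|---|
| 20% | 0.30/0.80 = 37.5% | +17.5 points |
| 30% | 0.20/0.70 = 28.6% | +8.6 points |
| 40% | 0.10/0.60 = 16.7% | −3.3 points |
| 45% | 0.05/0.55 = 9.1% | −10.9 points |

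The 20-min group is 100% open at that check by construction. Under this reading, grouping by dose conditions on the outcome.

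**Precision of a sound version.** With tiers defined in both arms, at 20% versus 50% and two-sided alpha 0.05 (normal approximation), power to detect the effect within one tier is about 23% with 8 per arm, 35% with 13 and 51% with 20. The tier sizes are assumptions.

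**The case against.** The strongest reply is that the article already says what it means by different doses. Randomization and intervention uses that phrase for the three rates, and the rates do not depend on the 20-minute angiogram. A reader might infer that the dose subgroup is outcome-dependent as planned. The text does not support that: only duration, and hence total dose, depends on the 20-minute result, and neither is a listed factor. Even under the total-dose reading, the 100% refers to the check during the procedure. The primary end point is graded on end-of-procedure runs and adjudicated by a blinded central laboratory, and it could differ. This part of the reply stands, so the outcome-dependence point is conditional.

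A reader might also infer that no subgroup by dose could ever be valid. That is too strong. The tier a patient qualifies for can be assigned to controls as well, and the table above shows that same-tier comparison recovers the true effect. This also stands, and it is the basis of the fix.

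A third reply is that coding details belong in an analysis plan that is not shown, and that the article gives no cut-points for age or NIHSS either. This succeeds only in part. A missing cut-point leaves a usable factor to be completed. Delivered TNK dose is a stated factor that cannot be applied to controls, so it has to be replaced and not merely detailed.

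**Conclusion.** The concern holds in limited form. As written, the dose factor is undefined for controls. If it is used as delivered rate, any comparison between doses, or of each dose with all controls, is confounded by intravenous thrombolysis and angioplasty/stenting. In the illustration, a constant 30-point effect appears as 38, 28 and 18 points. That size depends on the assumed tier shares and control rates; that the rate is set by the two other treatments is stated in the article. If dose were instead total dose or infusion time, it would also depend on the 20-minute result, and the 30-min group would show about 37.5% down to 9% success for an assumed 20% to 45% open by then.

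This is minor. It concerns one of nine subgroup factors, and the primary comparison and the sample size are untouched.

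**What to change.** In Statistical analysis, replace the dose factor with the dosing tier each patient qualifies for, defined identically in both arms: neither, one or both of intravenous thrombolysis and rescue angioplasty/stenting. Use status recorded at or before randomization. This condition is needed because the article does not say that angioplasty/stenting always precedes randomization, and status acquired afterwards could itself be affected by allocation.

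Test the arm-by-tier interaction in the logistic model already planned for the primary end point, and label it exploratory given the low power within tiers. Note that it overlaps with the separate subgroup by intravenous thrombolysis, which is one of the two components of the tier. Report delivered dose and infusion time descriptively in the TNK arm, with no efficacy comparison by dose.

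The cost is one sentence, and recording angioplasty/stenting status at randomization in both arms if it is not already captured. No dosing rule is affected.
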